### Safety aspects

Potential risks to the participant are minimal. There is potential for inconvenience because the young person is invited to take part in a treatment that will involve a time commitment. The potential for inconvenience will be minimised by virtue of the online nature of the treatment: young people can decide when and where are most convenient for them to complete treatment modules. Young people are free to withdraw from the study at any time.

In principle, there is potential for distress while completing OSCA. The likelihood of this is low because the program is goal-oriented in nature; young people did not become upset receiving the treatment in our previous case series. We will minimise this risk by fully explaining the nature of the program to young people. The young person is free to withdraw from the project at any time. In our pilot case series none of the adolescents who were treated showed an overall deterioration in their symptoms. Instead, everyone showed some benefit. This is consistent with the findings from our adult trials. We therefore consider the risk of symptom exacerbation to be low. Weekly measures of social anxiety and depressed mood will be taken and so any signs of deterioration will be detected quickly in the unlikely event that this should occur. An item assessing risk to self will be inserted into the SMFQ from the long version of the scale (item 19). Scores on this item will be reviewed weekly by the therapist to monitor levels and changes in risk. If signs of deterioration or an elevation in risk are identified, then the young person will be contacted and the appropriate procedures will be followed. An aim of the OSCA trial is to examine the safety of the treatment. We will do this in two ways. Adverse events (any untoward occurrence in an individual to whom the intervention has been administered, including occurrences which are not necessarily caused by or related to that therapy) will be monitored and recorded from randomisation to the final follow-up at 6 months. We will also assess reliable deterioration on the LSAS-CA-SR (our primary outcome measure).

Half of the participants will be randomly allocated to the waitlist condition. During this 14-week period the only contact they will have with the research team is at the midwait stage when they will be asked to complete questionnaires. It is possible that participants in the waitlist condition will require treatment during this period. Participants and their parents will be advised that they should seek services and help as required.

The online treatment programme has numerous security features representing current best practice and complies with NHS data security standards. It employs secure client-server communication, full encryption of the server database, enforcement of strong passwords, two- factor authentication and hosting on a tier 4 hosting server. External access to the database using SSH protocol is prohibited. The system has been subjected to industry-standard penetration testing. Online data are secured by encryption to prevent access from outside parties. Access to the server data by the software company hosting the online therapy programmes (FRY-IT) is protected by non-disclosure agreements and the Data Protection Act (1998).

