## Methods/design

### Design

The study is a two-arm RCT conducted in secondary schools in the United Kingdom (UK). The experimental arm is Online Social anxiety Cognitive therapy for Adolescents (OSCA). The comparison arm is waitlist. All participants will be assessed three times: at baseline (pretreatment/wait), midtreatment/wait (week 8) and posttreatment/wait (week 15). Participants in the experimental arm will also be assessed at 3- and 6-month follow-up. Postwait, participants in the waitlist arm will be offered OSCA. Assessments will be undertaken with parents as well where possible. Figure 1 shows the trial flow diagram. The trial has received approval from the University of Oxford Medical Sciences Division Research Board and it has been prospectively registered (http://www.isrctn.com/ISRCTN15079139).

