### Statistical analysis

All analyses will be intent-to-treat. No interim analyses are planned. Outcomes will be compared with hierarchical linear modelling. Time (midwait/midtreatment and postwait/posttreatment), treatment condition (OSCA, waitlist) and the time–condition interaction will be specified as categorical fixed factors, with baseline LSAS and gender as fixed covariates and participant as a random effect to account for between-person variation. Exploratory analyses using linear mixed effects models for each step to account for the nested data structure [43] will test for mediation of OSCA on social anxiety symptoms at posttreatment through candidate process variables from the cognitive model. Baseline outcomes will be included as predictors in all models. Categorical outcomes (response, remission, deterioration and diagnostic status) will be analysed using logistic regression, with treatment condition as the independent variable and baseline LSAS score and gender as covariates.

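### Adverse events are defined only for participants given OSCA although recorded from randomisation, and scheduled contact differs by arm, so adverse event rates would not be comparable with waitlist

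*Protocol article*

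**What the plan says.** Under Safety aspects the protocol article states: "An aim of the OSCA trial is to examine the safety of the treatment. We will do this in two ways".

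- **First measure: adverse events.** These are defined as "any untoward occurrence in an individual to whom the intervention has been administered". The definition expressly takes in events unrelated to the therapy. They "will be monitored and recorded from randomisation to the final follow-up at 6 months".
- **Second measure: reliable deterioration on the LSAS-CA-SR.** The Statistical analysis section covers it: "Categorical outcomes (response, remission, deterioration and diagnostic status) will be analysed using logistic regression, with treatment condition as the independent variable".

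On contact, the Interventions section gives OSCA participants a weekly therapist call for 14 weeks. The Abstract adds weekly measures for that arm, and Safety aspects adds a weekly therapist review of the risk item. For waitlist during the wait, Safety aspects says "the only contact they will have with the research team is at the midwait stage". The Design section schedules both arms at baseline, week 8 and week 15, and only the experimental arm at 3 and 6 months. Waitlist participants are offered OSCA after the postwait assessment.

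**The concern.** The definition covers people who have received the intervention, while the recording window opens before anyone has received it. A waitlist participant before crossover meets the window but not the definition. So does someone allocated to OSCA who never starts.

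This matters because the definition includes unrelated events. OSCA counts will therefore contain the ordinary background of illness, distress and mishap in this age group. The concurrent waitlist arm is the only part of the design that can show how much of the count is background, and the definition as worded removes it.

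Even with the definition widened, the two arms would not have equal opportunity for events to come to light. The schedule gives OSCA far more occasions for contact, and a longer planned follow-up that waitlist does not have.

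**Working it through.** The article states no adverse event rate or safety sample size, so there is no safety figure to reproduce. The check sets the definition, window and schedule side by side by arm, then illustrates the size.

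**Inputs from the article**
- Total 40, allocated 1:1 (Sample size; Recruitment and randomisation): 40 / 2 = 20 per arm.
- Weekly calls over 14 weeks, OSCA only (Interventions).
- Common assessments after baseline at weeks 8 and 15 (Design).
- 3- and 6-month visits, OSCA only (Design).

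**Step 1. Who can have an adverse event?**

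| Period | OSCA | Waitlist |
|---|---|---|
| Randomisation to start of OSCA | in window, outside definition | in window, outside definition |
| Start of OSCA to week 15 | in window and definition | in window, outside definition |
| After week 15 | in window and definition, visits to 6 months | inside definition only if OSCA is taken up; no 3- or 6-month visit scheduled |

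Over the randomised period the countable waitlist events are 0, whatever happens.

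**Step 2. Size under the literal definition.** Let p be the true proportion with any untoward event by week 15, the same in both arms. This is an assumption. Suppose also that all 20 OSCA participants start and that every event is detected. The expected countable number in OSCA is 20 × p.
- p = 10%: 20 × 0.10 = 2, against 0
- p = 20%: 20 × 0.20 = 4, against 0
- p = 40%: 20 × 0.40 = 8, against 0

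**Step 3. Scheduled contact if the definition is widened.** After baseline to week 15, OSCA has about 14 calls plus 2 assessments, 16 in all, and weekly online measures besides. Waitlist has 2 (weeks 8 and 15).

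The article does not say how adverse events are elicited, so the effect on detection is an assumption. Take equal true risk and 95% detection in OSCA. The apparent risk ratio is 0.95 / (waitlist detection):
- 25%: 0.95 / 0.25 = 3.8
- 50%: 0.95 / 0.50 = 1.9
- 75%: 0.95 / 0.75 = 1.27
- 100%: 0.95 / 1.00 = 0.95

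At p = 20% the expected recorded counts are 20 × 0.20 × 0.95 = 3.8 in OSCA, against 1.0, 2.0, 3.0 or 4.0 in waitlist.

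**Step 4. Observation time.** If the six months run from posttreatment (assumed), OSCA is observed for about 15 + 26 = 41 weeks, against 15 weeks of untreated waitlist. The ratio of totals is 41 / 15 = 2.7. The extra time is 26 / 15 = 1.7 times the randomised period.

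**Step 5. The second safety measure.** The primary outcome scale is scheduled on the common timetable for both arms, and deterioration is modelled with condition as the independent variable. It therefore yields a rate out of about 20 in each arm. It records worsening social anxiety and no other kind of untoward event.

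**The case against.** The strongest reply has four parts.

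1. **The safety aim does have a controlled comparison.** A reader might infer from the adverse event definition that the aim as a whole has no waitlist rate. The article does not support that: reliable deterioration is the second stated measure and is compared by arm. This stands, and it confines the point to adverse events. It does not repair them, because a symptom score cannot stand in for other untoward events.

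2. **Nothing says adverse events are found through the weekly contact.** A reader might infer it. However, the weekly review described concerns symptom measures and the risk item. Elicitation may be set out in the full protocol, and Table 1 and Fig. 2 could not be read in the copy available for this review. This also stands. Unequal detection is an inference from the contact schedule, and the missing description of elicitation is not itself a fault.

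3. **No between-arm comparison of adverse events is planned.** The categorical outcomes listed for logistic regression do not include them, so a misleading contrast of six-month OSCA counts with 15-week waitlist counts is not something the article proposes. This is correct. What is lost is the ability to interpret the OSCA count against background.

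4. **Recording from randomisation, and the intention-to-treat statement, suggest that all randomised participants were meant.** That is plausible. If so, the definition contradicts the intention and the two need reconciling, which is what is asked for.

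**Conclusion.** The point holds for one of the two stated safety measures. The definition and the recording window do not fit together. Followed literally, the definition gives a pre-crossover waitlist count of zero at any true rate. This conclusion needs no assumption beyond reading the definition as written. The illustrative contrast of 2 to 8 against 0 rests on an assumed risk of 10% to 40%, full detection and all 20 OSCA participants starting.

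That rates would remain non-comparable after a simple rewording rests on the contact and follow-up schedule. The size is unknown: on the assumed detection values the apparent risk ratio runs from 0.95 to 3.8 with no true difference. The observation-time ratio of about 2.7 is a ratio of totals, depends on where the six months start, and matters only if whole-study counts were compared.

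LSAS-CA-SR deterioration is comparable between arms and is unaffected, as are the efficacy analyses. The change should be made because safety is a declared aim and the adverse event half of it cannot be interpreted against background as written.

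**What to change.** - Reword the definition so that an adverse event is any untoward occurrence in any randomised participant, counted from randomisation and whether or not OSCA has been started.
- Ask the same structured adverse event question in both arms at the existing week-8 and week-15 assessments, and compare arms on those answers over weeks 0–15 only.
- Report events that surface through OSCA weekly contact, in the 3- and 6-month follow-up, or after waitlist crossover in a separate table labelled as uncontrolled.

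If the full protocol already asks both arms alike at weeks 8 and 15, only the definition and the reporting rule need changing.

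The cost is a reworded sentence and one added question at two assessments, with slightly more questionnaire burden for participants. With about 20 per arm the comparison will be imprecise and should be presented descriptively. No treatment or clinical management changes.

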### Service user involvement

Young people, both healthy school pupils and service users, have been involved in all stages of the project. Service users have been involved in the development of the questionnaires and the worksheets used to support face-to-face Cognitive Therapy and OSCA. Young people have provided detailed advice on how to adapt adult online Cognitive Therapy for young people. Pupils have advised on how best to recruit young people in schools. A small group of young people have requested to remain involved in a consultation role throughout the trial.

## Discussion

Given the prevalence of social anxiety in adolescents and the very limited number of child therapists in the NHS, we are faced with the challenge of developing effective, scalable treatments. Here, we describe the protocol for a RCT that aims to examine the efficacy of a newly developed online version of Cognitive Therapy for SAD in adolescents (OSCA) compared to waitlist control. If superiority of OSCA can be demonstrated, this will have important implications for treatment provision.

The majority of adolescents with SAD are not accessing services despite experiencing high levels of symptoms and impairment [24]. There may be a number of reasons for this, including perceived stigma and shame, a lack of understanding of the care system or a shortage of appropriate CAMHS services. Two aspects of the OSCA trial design have the potential to overcome at least some of these obstacles and improve outcomes for socially anxious young people.

Using the Internet to delivery therapy provides a number of practical advantages over face-to-face therapy, including reduced therapist and clinic burden and high treatment fidelity. In addition to this, as highlighted in the recent Government Green Paper (2017), schools may provide an ideal setting to intervene early in youth mental health difficulties, potentially overcoming various obstacles to accessing care. For example, it would sidestep the potential issue of underdetection of SAD by primary care physicians [27]. Likewise, screening programs are likely to identify young people with SAD who have not sought help, for example due to feelings of shame, embarrassment or failure by family members to appreciate the severity of the problem. It would also reduce the burden and interference associated with attending appointments at a clinic.

## Conclusions

The aim of the trial is to determine whether OSCA, an Internet version of Cognitive Therapy for adolescent SAD delivered via schools, is effective compared to a waitlist control. Data about the acceptability of the treatment and suggestions for ways to improve OSCA will be sought from young people and parents. If the intervention is found to be effective compared to waitlist, then a future trial could compare the Internet intervention to face-to-face therapy, to examine clinical outcomes and costs. OSCA has the potential to improve the treatment outcomes and future prospects for adolescents with SAD, the majority of whom are not currently receiving treatment, as well as reduce the burden on over-stretched CAMHS services.

## Data Availability

After publication of the study results, the individual participant data will be made available via the Bodleian-ORA data repository. Data available will be research data reported in the publication, with the exception of data that could compromise participant anonymity.

## Abbreviations

ADIS-C/P: Anxiety Disorders Interview Schedule for Children and Parents
ASAQ: Adolescent Social Attitudes Questionnaire
ASBQ: Adolescent Social Behaviour Questionnaire
ASCQ: Adolescent Social Cognitions Questionnaire
CAMHS: Child and Adolescent Mental Health Service
CBT: Cognitive behaviour therapy
CONSORT: Consolidated Standards of Reporting Trials
DSM-5: Diagnostic and Statistical Manual of Mental Disorders, 5th edition
LSAS-CA-SR: Liebowitz Social Anxiety Scale for children and adolescents self-report version
Mini-SPIN: Mini Social Phobi Inventory
NICE: The National Institute for Health and Care Exellence
OSCA: Online Social anxiety Cognitive therapy for Adolescents
RCADS: Revised Children’s Anxiety and Depression Scale
RCT: Randomised controlled trial
SAD: Social anxiety disorder
SMFQ: Short Mood and Feelings Questionnaire
SPIRIT: Standard Protocol Items: Recommendations for Interventional Trials
WAI: Working Alliance Inventory
